Telemedicine has the potential to improve access to PR and support long-term exercise maintenance strategies. Telerehabilitation is the use of information and communication technologies to provide rehabilitation services remotely to people in their homes or other environments [21]. In contrast to traditional centre-based programmes, undertaking PR within the home environment may promote more effective integration of exercise routines into daily life over the longer term [22]. Evidence of the use of telemedicine in PR is still limited [13]. A recent review showed that telemedicine was effective in increasing physical activity levels in patients with COPD [23]. A few studies, most of which uncontrolled, showed promising results for short-term telerehabilitation interventions in regards to feasibility, safety, exercise capacity, and health-related quality of life [24–29]. However, only one uncontrolled pilot study trialled a long-term telerehabilitation intervention for patients with COPD [30]. This study demonstrated positive outcomes in terms of exercise maintenance, physical performance, health status and quality of life [31]. Importantly, long-term adherence was supported by experienced health benefits, self-efficacy, emotional safety, and maintenance of motivation [32]. Larger controlled trials are needed to explore the long-term effects of telerehabilitation in COPD.

Developing new cost-effective ways to sustain regular exercise over the long term and broaden the applicability and availability of PR is an important goal in the COPD management. The aim of this study is to compare long-term telerehabilitation of COPD patients consisting of exercise training at home, telemonitoring, and self-management, with unsupervised exercise training at home and with standard care. We hypothesised that long-term telerehabilitation will reduce the number of hospital readmissions and improve patient’s level of physical activity, health status and quality of life. The results from this study will provide decision makers, as well as practitioners, evidence on whether telerehabilitation interventions might be added to the current offer of traditional PR programmes and maintenance strategies.

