### Outcome measures

The primary outcome is the combined number of hospitalisations and ED presentations. Differences in the rate of events between the study arms will be measured at all assessment time points (Table 2). Data on hospitalisations and ED presentations, together with outpatient visits, will be collected from hospitals records (in Australia), regional systems (in Denmark) and national registries (in Norway). Details will include institution, date of admission, date of discharge, diagnosis-related group (DRG), diagnoses, procedures and associated cost. In addition, use of hospital resources will be recorded during the follow-up visits. Hospitalisations and ED presentations will be also analysed separately as secondary outcomes. Mortality will be monitored along the study together with dropouts.

**Table 2 Tab2:** Primary and secondary outcomes and related measures

Outcome	Measure
Primary outcome	
• Combined number of hospitalisations and ED presentations	• Incidence Density
Secondary outcomes	
• Hospitalisations • ED presentations • Mortality • Time free from first event • Health status • Quality of life • Anxiety and depression • Self-efficacy • Subjective impression of overall change • Physical performance • Level of physical activity	• Incidence Density • Incidence Density • Mortality rate • Days to first hospitalisation or ED presentation • COPD Assessment Test • EQ-5D • Hospital Anxiety and Depression Scale (HAD) • Generalised Self-Efficacy Scale (GSES) • Patient global impression of change scale (PGIC) • 6-min walking distance (6MWD) • Daily number of steps, minutes of moderate to vigorous physical activity and sedentary time during 1-week
• Cost-effectiveness • Experiences in telerehabilitation	• Cost-utility analysis (cost-per-QALY) • Qualitative interviews with semi-structured questions

Health status will be measured with the COPD Assessment Test (CAT) [37]. Health-related quality of life will be measured with the EQ-5D questionnaire [38]. Levels of anxiety and depression will be measured with the Hospital Anxiety and Depression Scale (HAD) [39]. Self-efficacy will be measured with the Generalised Self-Efficacy Scale (GSES) [40]. Subjective impression of overall change will be measured with the Patient global impression of change scale (PGIC) [41]. The study questionnaires, available in English, Norwegian and Danish with validated versions, will be collected along the study at different time points (Table 1).

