### Statistical analysis

Descriptive statistics at baseline will be reported as means ± SD for normally distributed continuous variables, or medians with 25–75th percentiles in the case of skewed distribution. Normality of distribution will be tested by means of the nonparametric Kolmogorov-Smirnov test. An intention-to-treat analysis will be performed on all randomised subjects to provide unbiased comparisons among groups and avoid the effects of dropout. The primary outcome and related secondary outcomes will be measured through the Incidence Density, defined as the number of events in a group divided by the total person-time accumulated during the study in that group [44]. Differences between study arms will be tested by the Comparison of Incidence Rates. A two-sided test and a significance level of *α* = 0.05 will be used. All events from the day after randomisation to patient exit/death will be included. Other secondary outcomes will be measured as changes from baseline to all assessment time points. Changes of the secondary outcomes will be tested by use of linear mixed models, which allow accounting for repeated measures collected in a longitudinal design. Moreover, linear mixed models deal better with dropouts that other methods used for repeated measures, and use of imputation techniques for missing data is not necessary. A *p*-value <0.05 will be considered significant for all tests. All statistical analyses will be performed by using IBM SPSS Statistics.

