### Sample size

The sample size requirements for this study were intended to provide adequate power for the analysis of the primary outcome. From studies with patients with similar characteristics [45–48], we estimated an incidence density used as a null hypothesis of 2 events per person-year, and a 40 % relative reduction in the primary outcome. In a major study of a management programme including home exercises for COPD patients after acute exacerbations [46] the mean number of hospital admissions per patient was reduced from 1.6 to 0.9 in the year following a hospital admission. We calculated that a sample size of 65 person-years per group would allow a power of 95 % to detect an incidence rate ratio of 0.60, with a type-I error (α) of 0.05. Assuming that up to 20 % of patients may drop out uniformly over the intervention period, 40 patients (corresponding to 80 person-years) will be enrolled per each of the three arms for the 2-year study duration. In total, 120 patients (corresponding to 240 person-years) will therefore be enrolled in the study. Recruitment is expected to be concluded by the end of 2016.

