## Discussion

This study protocol described the methods used in this first RCT investigating the effects of long-term telerehabilitation in COPD. Patients with COPD often experience repeated exacerbations which lead to a worsening of their health condition and to hospital admissions [3]. Moreover, hospital readmissions are more likely to occur in patients with prior history of hospitalisations [5]. There is an increasing need for cost-effective treatment strategies for patients with COPD [22]. PR is a low-cost, integral component of COPD management [12]. PR is traditionally centre-based and offered either as a 6–12-week outpatient programme or as a 4-week inpatient programme. Available resources for PR are often limited, and patients living in rural areas especially suffer from poor availability of PR programmes [49]. Maintenance strategies are needed to sustain the benefits of PR over the long term [15]. However, these are scarcely documented, and the optimal combination of maintenance interventions after completion of a PR programme remains unknown [12]. Long-term telerehabilitation is an innovative intervention which might reduce hospital readmissions in COPD and thus limit healthcare utilisation. The results of this study will provide evidence on whether long-term telerehabilitation represents a cost-effective strategy for the follow-up of patients with COPD. The delivery of telerehabilitation services will also broaden the availability of PR and maintenance strategies, especially to those living in remote areas and with no access to centre-based exercise programmes.

Significant improvements in outcomes can be obtained with both supervised and unsupervised home exercise [50]. However, sustaining long-term exercise is generally difficult [17] for many reasons, including professional support, regular supervision [16], emotional safety, and maintenance of motivation [32]. We expect that standard care and unsupervised home exercise will be less beneficial than a telerehabilitation intervention where patients are supervised regularly by a physiotherapist via videoconferencing. The study was designed as a three-armed RCT to isolate the effects of placing training equipment in the patient’s home from those of telemonitoring.

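### Two unranked telerehabilitation contrasts each get their own 0.05 on the primary outcome, while the trial is sized for one unnamed contrast: about 9% false-positive risk and no rule for success

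*Protocol article*

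**What the plan says.** All references are to the protocol article.

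- **Aim (Background).** Telerehabilitation is to be compared "with unsupervised exercise training at home and with standard care". One hypothesis follows, that telerehabilitation reduces readmissions. Neither comparator is put first.
- **Discussion.** "We expect that standard care and unsupervised home exercise will be less beneficial than a telerehabilitation intervention". The same paragraph gives the reason for three arms: to separate the effect of having the equipment at home from that of telemonitoring.
- **Statistical analysis.** For the primary outcome, "Differences between study arms will be tested by the Comparison of Incidence Rates". The level is set by "A two-sided test and a significance level of" 0.05, and the section later states that a p-"value <0.05 will be considered significant for all tests". The measure is events divided by person-time accumulated over the study, and "All events from the day after randomisation to patient exit/death will be included".
- **Outcome measures.** "Differences in the rate of events between the study arms will be measured at all assessment time points". Table 1 puts the follow-up assessments at 6 months, 1 year and 2 years.
- **Sample size.** 65 person-years per group give 95% power "to detect an incidence rate ratio of 0.60" at α 0.05, from a rate of 2 events per person-year. No pair of arms is named.

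**The concern.** The α of 0.05 in the sample size calculation describes one test. The analysis rule grants 0.05 to every test, and the aim calls for at least two on the primary outcome. Both contrasts share the telerehabilitation arm, address the same hypothesis and feed the same decision: whether to add telerehabilitation to current services. If either may be claimed on its own, the error rate for that decision is above 0.05.

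There is also a gap in interpretation. Suppose telerehabilitation beats control but not treadmill, or the reverse. The article does not say whether such a trial met its primary objective, so the answer could be chosen after the results are known.

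**Working it through.** **1. Reproduce the planned size.** Inputs from Sample size: control rate 2.0 per person-year, 40% reduction (1.2 per person-year), α 0.05, power 95%. Two-sided testing comes from Statistical analysis. For one pair of Poisson rates:

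T = (1.960 + 1.645)² × (2.0 + 1.2) / (2.0 − 1.2)² = 12.995 × 3.2 / 0.64 = 64.97

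This is the stated 65 person-years per group. The figure is right for a single two-sided test and contains no allowance for a second contrast.

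**2. Error over the two stated contrasts.** Assume no true effect. With equal arms, the two test statistics share the telerehabilitation arm and so have correlation 0.5. Then:

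- P(both two-sided p < 0.05) = 0.0093
- P(at least one) = 0.05 + 0.05 − 0.0093 = 0.0907, about 9%

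In the direction favouring telerehabilitation only:

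- P(both) = 0.0046
- P(at least one) = 0.025 + 0.025 − 0.0046 = 0.0454

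Simulated Poisson counts (2 events per person-year, 65 person-years per arm, Wald test on the log rate ratio) give 8.9% two-sided. In favour of telerehabilitation they give 4.4% for either contrast, 2.4% for one given contrast (nominal 2.5%) and 0.5% for both. At 72 person-years, which is 80 × (1 − 0.20/2) under the stated uniform 20% dropout, the two-sided figure is 9.0%.

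**3. If treadmill versus control is tested too.** Three pairs give 12.2% by normal theory and 12.0% in the simulation.

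**4. If 6 months and 1 year were also tested for significance.** With cumulative data at 0.5, 1 and 2 years:

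| Chance of at least one p < 0.05 | 2-year analysis only | All three assessments |
|---|---|---|
| Two telerehabilitation pairs | about 9% | 19–20% |
| All three pairs | about 12% | 25–26% |

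The spread in the last column comes from the choice of test statistic and the dropout pattern.

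**5. What an ordered test costs.** Telerehabilitation rate 1.2, control 2.0, 65 person-years per arm, simulated. The treadmill rate is an assumption, since the article gives none.

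| Assumed treadmill rate | Power vs control (first test) | Power vs treadmill, tested freely | Power vs treadmill, only after the first succeeds |
|---|---|---|---|
| 2.0 (no effect) | 95.2% | 95.2% | 91.5% |
| 1.8 (10% effect) | 95.2% | 79.9% | 77.8% |
| 1.6 (20% effect) | 95.2% | 48.5% | 47.9% |

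Splitting α instead (0.025 for each of the two contrasts) takes power for a rate ratio of 0.60 at 65 person-years from 95.0% to 91.4%.

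**The case against.** The best reply has four parts.

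*The two contrasts ask different questions.* One concerns the whole package and the other supervision beyond equipment. Each keeps its own 5% error, and whether to adjust across distinct questions in a multi-arm trial is a matter of judgement. That is a respectable position, but the article attaches one hypothesis to both contrasts. Even without adjustment, it would still need to say which contrast decides success, or whether both must.

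*Testing order belongs in the analysis plan, and this is a condensed article.* Silence alone would be no finding. Here, however, the article states a rule, significance at 0.05 for every test, next to a size calculation that relies on 0.05 for one. The rule does not forbid an order or adjusted p-values, but it supplies neither.

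*The time point is fixed.* A reader might infer from Outcome measures that the primary outcome is tested three times and that the error is therefore about 1 in 4. The text does not support that. Differences are to be measured, not tested, at each assessment. Statistical analysis defines the rate over person-time for the whole study, and the size rests on 2-year person-time. This objection stands: the 19–26% range applies only if the earlier assessments are also tested for significance.

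*Treadmill versus control is outside the aim.* This also stands. The three-arm rationale in the Discussion implies an interest in it, but neither the aim nor the stated expectation includes it. The 12% figure, about 1 in 8, is therefore secondary to the 9%.

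**Conclusion.** The point holds in limited form. The 65 person-years is correct for one comparison. The defect is that the article does not say which comparison, and then lets two unranked contrasts of one hypothesis each count at 0.05. The chance of at least one false-positive primary result is about 9% two-sided, or about 4.4% in favour of telerehabilitation against 2.5% nominal for a single test. It is about 12% two-sided if the implied third pair is tested. Nothing states whether one or both contrasts must succeed.

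A reader might also infer that multiplicity will often leave the two contrasts in conflict. Exactly one of them is significant in about 7%, 19% or 48% of trials for treadmill effects of 0, 10% or 20%. Those effects are assumed, and the 48% mostly reflects low power for 1.2 versus 1.6 events per person-year (48.5%). An ordered test settles how such a result is read, but does not raise that power.

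The error figures assume no true effect, equal arms and Poisson counts without extra variation between patients, that is, a test with the correct size for a single pair.

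**What to change.** In Statistical analysis and Sample size, state that:

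1. The primary test is telerehabilitation versus control over the full 2-year follow-up, two-sided α 0.05, and the rate ratio of 0.60 refers to this pair.
2. Telerehabilitation versus treadmill is tested at two-sided 0.05 only if the first test is significant.
3. Treadmill versus control, and the 6-month and 1-year comparisons, are reported as rate ratios with 95% confidence intervals and carry no significance claim for the primary outcome.
4. The 0.05 rule for all tests applies to secondary outcomes only, labelled as unadjusted.

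This returns the error for the two telerehabilitation claims to 5%. Enrolment is unchanged, and the Trial status section says recruitment is still under way, so the change can be made before results are known. The first test keeps its 95% power. Telerehabilitation versus treadmill loses up to about 4 points (95.2% to 91.5% with no treadmill effect, less otherwise), and treadmill versus control gives up any confirmatory claim. Putting control first is a choice. If the sponsor sees supervision beyond equipment as the main question, the order can be reversed, provided it is fixed in advance.

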### Sample size

The sample size requirements for this study were intended to provide adequate power for the analysis of the primary outcome. From studies with patients with similar characteristics [45–48], we estimated an incidence density used as a null hypothesis of 2 events per person-year, and a 40 % relative reduction in the primary outcome. In a major study of a management programme including home exercises for COPD patients after acute exacerbations [46] the mean number of hospital admissions per patient was reduced from 1.6 to 0.9 in the year following a hospital admission. We calculated that a sample size of 65 person-years per group would allow a power of 95 % to detect an incidence rate ratio of 0.60, with a type-I error (α) of 0.05. Assuming that up to 20 % of patients may drop out uniformly over the intervention period, 40 patients (corresponding to 80 person-years) will be enrolled per each of the three arms for the 2-year study duration. In total, 120 patients (corresponding to 240 person-years) will therefore be enrolled in the study. Recruitment is expected to be concluded by the end of 2016.

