## Background

Chronic obstructive pulmonary disease (COPD) is characterised by a persistent airflow limitation that is usually progressive [1]. Patients experience frequent acute exacerbations, characterised by worsening of respiratory symptoms [2] which may lead, in the worst cases, to a hospital admission [3]. COPD poses a substantial burden on healthcare budgets. The largest part of the health service expenditure is for hospitalisations and emergency department (ED) presentations, which commonly occur in the latter stages of the disease [4]. Moreover, prior hospitalisations represent a risk factor for rehospitalisation in patients discharged after a severe exacerbation [5]. Hospital admissions for exacerbations do not only represent a burden for the healthcare system, but have also a negative impact on patients, who experience reduced physical activity, decreased exercise performance [6], and impaired quality of life, even in mild stages of the disease [7]. Dyspnoea, the most commonly reported symptom during acute events, is associated with anxiety and depression [8]. Importantly, reduced physical activity is the strongest predictor of mortality in patients with COPD [9].

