## Methods/Design

### Design

An international multicentre randomised controlled trial (RCT) conducted across sites in three countries (Norway, Australia, and Denmark), where 120 patients with COPD are randomly assigned to three arms (telerehabilitation, treadmill, control) in a 1:1:1 ratio and followed up for 2 years. The trial is restricted to patients who have volunteered and provided written informed consent in accordance with the Declaration of Helsinki. The trial received approval from the Regional Committee for Medical and Health Research Ethics in Norway (2014/676/REK nord), the Alfred Hospital Human Research Ethics Committee (289/14), and the North Denmark Region Committee on Health Research Ethics (N-20140038). The protocol of this RCT fulfils the Standard Protocol Items: Recommendations for Interventional Trials (SPIRIT) guidelines (Additional file 1).

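### The 95 % power for 65 person-years per group assumes that all patients in an arm share one event rate; with unequal risk between patients, which the protocol itself describes, the figure is overstated

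*Protocol article*

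**What the plan says.** All references are to the protocol article.

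- **Sample size.** The starting point is "an incidence density used as a null hypothesis of 2 events per person-year", and the trial is sized "to detect an incidence rate ratio of 0.60". The result reads: "We calculated that a sample size of 65 person-years per group would allow a power of 95" %. Allowing for up to 20 % dropout spread evenly over time, the plan enrols 40 patients per arm, counted as 80 person-years. No between-patient variance or dispersion appears.
- **Statistical analysis.** The primary measure is "the number of events in a group divided by the total person-time accumulated during the study in that group", and arms are compared on these pooled rates. The error rate is fixed by "A two-sided test and a significance level of" 0.05.
- **Design.** Patients are allocated "in a 1:1:1 ratio and followed up for 2 years".
- **Background.** The authors note that "prior hospitalisations represent a risk factor for rehospitalisation in patients discharged after a severe exacerbation", and the Discussion repeats the point. Eligibility criteria admit moderate to very severe airflow limitation and anyone with one or more COPD-related admissions or ED visits in the previous year. Randomisation is stratified by severity.

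**The concern.** Hospitalisations and ED visits recur within patients, and some patients are more prone to them than others. The information on a rate ratio then depends on the number of patients as well as on total person-time. Forty patients followed for 2 years are not equivalent to 80 followed for 1 year, because the between-patient part of the variance does not shrink with longer follow-up. A calculation expressed purely in person-years leaves that part out.

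The stated power is the only justification given for 40 patients per arm on the primary outcome. If it is too high at a true two-sided 5 % level, readers will credit the trial with more sensitivity to a 40 % reduction than it has. If the primary test makes the same assumption, its false-positive rate is above 5 % as well.

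**Working it through.** **Inputs from the article.** Control rate λ0 = 2.0 per person-year; rate ratio 0.60, so λ1 = 1.2; two-sided α = 0.05; 40 patients per arm; 2 years' follow-up; up to 20 % uniform dropout.

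**Assumed input.** Negative binomial dispersion k, varied from 0 to 1. The article gives no value.

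**1. Reproduce the plan's figure.** Poisson rate-difference formula:

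T = (1.960 + 1.645)² × (2.0 + 1.2) / (2.0 − 1.2)² = 64.97 person-years per group.

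Power at 65 person-years is 95.0 % by this formula and 94.6 % on the log rate-ratio scale. A one-sided test does not fit, since it needs only 54 to 55 person-years. The stated figure is therefore the two-sided Poisson result.

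**2. Person-time that 40 patients yield.** Literally uniform dropout of 20 %: 32 × 2 + 8 × 1 = 72 person-years. No dropout: 80. The stated requirement: 65. All three are carried forward.

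**3. Add between-patient variation.** With mean follow-up t = T/40:

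SE² = [1/(2.0t) + 1/(1.2t) + 2k] / 40, and power = Φ(0.5108/SE − 1.96), where 0.5108 = −log 0.60.

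The term 2k/40 does not depend on t. Example at T = 65 (t = 1.625), k = 0.5: SE² = (0.3077 + 0.5128 + 1.0)/40 = 0.0455, SE = 0.213, power = 67 %.

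| k (assumed) | 65 person-years | 72 | 80 |
|---|---|---|---|
| 0 | 94.6 % | 96.4 % | 97.7 % |
| 0.1 | 89 % | 91-92 % | 93-94 % |
| 0.25 | 80 % | 83 % | 85 % |
| 0.5 | 67 % | 69 % | 71 % |
| 1 | 49 % | 50 % | 51 % |

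Solving for power = 95 % gives k of about 0.03 at 72 person-years and 0.07 at 80; at 65 there is no slack. Power drops below 80 % once k exceeds about 0.25 (65 person-years) to 0.33 (80).

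Simulation (20,000 gamma-Poisson trials, 20 % uniform dropout, per-patient robust variance) agrees: 82 %, 68 % and 50 % at k = 0.25, 0.5 and 1.

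**4. Detectable rate ratio at 80 % power.** Solve −log(IRR) = (1.960 + 0.842) × SE, with λ1 = 2 × IRR inside SE. Over 65 to 80 person-years: about 0.60-0.62 at k = 0.25, 0.55-0.56 at k = 0.5 and 0.47-0.48 at k = 1.

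**5. The planned comparison, read as a Poisson test.** With both arms at 2.0 per year, the true variance exceeds the Poisson variance by the factor φ = 1 + kλE[t²]/E[t]. Under 20 % uniform dropout, E[t²]/E[t] = (0.8 × 4 + 0.2 × 4/3)/1.8 = 1.926, so φ = 1 + 3.85k. The actual type I error is 2Φ(−1.96/√φ). At k = 0.25, φ = 1.96, giving 16 %; at k = 1, φ = 4.85, giving 37 %. Simulation gives about 9 %, 16 %, 25 % and 37 % at k = 0.1, 0.25, 0.5 and 1. For a true rate ratio of 0.60 this test rejects in about 92 %, 88 % and 82 % of trials at k = 0.25, 0.5 and 1, but not at a 5 % level.

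**6. Is k = 0 credible here?** It would put every control patient at exactly 2 events per year, leaving exp(−4) = 1.8 % event-free over 2 years. For scale only: an arm split evenly between patients averaging 1 and 3 events per year has rate variance 1 and mean 2, so k = 1/2² = 0.25.

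**The case against.** The strongest reply is that nothing has been miscalculated. The figure follows from its inputs, and the complaint is about an unstated modelling assumption. That stands: this is not an arithmetic error.

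Second, a reader might infer that the trial's real power is 50 to 80 %. The documents do not support that. It requires k between about 0.25 and 1, and nothing in the article favours those values over k = 0.1, where power is still 89-94 %. The Background sentence on prior hospitalisation does not size the heterogeneity either. Every participant must already have had an admission or ED visit in the past year, so eligibility largely removes the yes/no contrast. Differences in the number of prior events and in severity remain, which supports heterogeneity in kind but not in amount.

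Third, it would be slightly too strong to say that 95 % holds only with zero variation. That is exact at 65 person-years; the 72 to 80 that may accrue leave slack, though only for very small k.

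Fourth, a reader might conclude that the main danger is a missed effect and an over-read null result. The lower power figures belong to an analysis that allows for overdispersion. The article plans a comparison of pooled rates, and if that is a Poisson test, the larger hazard as planned is a false positive. This objection also stands, and it means that restating the power alone would be incoherent.

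Finally, the change affects no patient and no trial procedure. That bears on cost. It does not rescue a definite power figure that rests on an assumption at odds with the article's own description of its patients.

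**Conclusion.** The point holds in limited form. The 95 % is correct arithmetic under a pure Poisson model and overstated, at a true two-sided 5 % level, once patients within an arm differ in risk. The size of the overstatement cannot be fixed from the documents: it is a few percentage points at k = 0.1, 10 to 15 points at k = 0.25 and about 45 points at k = 1. These results assume gamma-distributed patient rates with the same k in each arm, the planned rates of 2.0 and 1.2, and 40 patients per arm contributing 65 to 80 person-years. The type I error figures further assume that the comparison of incidence rates uses Poisson variance, the natural reading of a pooled events-over-person-time measure, though the article does not spell out the variance. With heterogeneity, the plan cannot have both its stated power and its stated α.

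**What to change.** Keep 120 patients and make two linked changes.

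1. **Sample size.** Replace the unqualified 95 % with power expressed per patient (40 per arm, expected mean follow-up) under a negative binomial model. Tabulate it over a stated range of assumed k, for example 0, 0.1, 0.25, 0.5 and 1, with the detectable rate ratio at 80 % power. State that 95 % is the no-heterogeneity case.
2. **Statistical analysis.** Change the primary test to match: negative binomial regression with log follow-up time as offset, or a rate ratio with per-patient robust variance. In the simulation the robust version held type I error at about 5.5 to 6 % for k = 0.25 to 1, so a small-sample correction is worth considering.

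If k is estimated from blinded pooled counts, allow for the between-arm difference, since k_pooled = (1 + k)(1 + CV²) − 1, where CV is that of the arm rates. Even at k = 0 the planned effect adds 0.0625 for arms at 2.0 and 1.2 (0.4²/1.6²), and about 0.05 for arms at 2.0, 2.0 and 1.2.

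The cost is a less favourable stated figure and slightly more analysis work.
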